##### Skin strain

The motion of the beads attached to the skin will be tracked using a custom software to identify the center of each bead in each pair of synchronized radiographs. This software finds bead centroids with an accuracy of 0.08 to 0.12 mm during dynamic movements [42, 43]. Skin strain will be calculated using freely available software (FEBio), with the zero strain value determined while wearing the socket but not bearing weight. Variability in the zero strain measurement will be determined by doffing and donning the socket three times and imaging the residual limb after each donning. The residual femur will be divided into 4 primary regions (anterior, medial, posterior, and lateral), with proximal and distal sub-regions within each region, resulting in 8 total regions. The average and peak skin strain within each region will be determined and expressed as a percentage of the gait cycle. The average values over all steps will be included as variables in the analysis for aims 1 and 2.

##### In-socket pressure

We will measure peak pressure and area under the pressure versus the time curve recorded by each in-socket pressure sensor. Pressure will be measured for up to 6 steps per walking trial (i.e., 18 steps per socket) and the pressure results expressed as a percentage of the gait cycle (Fig. 4B). The average values over all steps will be included as variables in the aim 1 and aim 2 analysis.

##### Plantar pressure

Pressure readings from each of the 99 discrete sensors will be used to calculate total plantar pressure (Fig. 13A) and the path of the center of pressure for each step (Fig. 13B). The peak plantar pressure from foot strike to midstance and the medial-lateral and anterior-posterior excursion of the center of pressure during support will be included in the aim 2 analysis.

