#### Specific aim 2: Identify readily available clinical measurements that are associated with residual femur motion, skin strain, and peak pressure within the socket during dynamic activities

Being able to quantify the parameters of interest in a research setting does not easily translate to clinical application. The purpose of this aim is to correlate our laboratory findings with measurements obtained by conventional clinical assessments. We hypothesize that the following clinical measurements correspond to dynamic in-socket mechanics: (H1) static imaging under different loads will correspond to dynamic residual femur motion, (H2) gait analysis will correspond to dynamic pressure distribution, and (H3) residual limb tissue compliance will correspond to peak skin strain.

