**Fig. 13 Fig13:**
[figure not shown]
Plantar pressure measurements. **A** Total plantar pressure during the support phase of gait for 6 steps. **B** The path of the center of pressure during gait over 6 steps, superimposed on an outline of the foot

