##### Body kinematics

Trunk lean and hip flexion/extension during gait will be calculated from the conventional motion capture system (marker-based) for at least 6 steps per trial of treadmill walking. Body angles will be calculated using markers placed on the shoulders, C7, hips (ASIS and PSIS), greater trochanters, knee (or flexion axis of the prosthesis), ankle, and foot. We will determine the average of peak trunk lean and the average peak hip flexion and extension over all steps and all trials for each prosthesis. The average values will be included in the aim 2 analysis. Qualitative gait analysis will be performed by 3 investigators using the webcam videos to classify the participant’s gait asymmetry in terms of magnitude and timing.

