## Statistical methods

### Statistical methods for primary and secondary outcomes {20a}

#### Aim 1

The effects of in-socket mechanics, such as residual bone motion, peak skin strain, and pressure distribution on both physical function and patient-reported outcomes will be assessed using a generalized linear model (GLM). We will examine the effect(s) of each in-socket mechanical parameter on outcomes by utilizing the type III sum of squares tables. If our sample size drops below 30, we will develop separate models for each of the parameters of interest and outcome. Finally, we will create a unified model, containing the statistically significant parameter coefficients, which will allow us to predict physical function and patient response based on the changes to the included parameter estimates.

#### Aim 2

We will use partial correlation to examine the association between residual femur motion, skin strain, pressure, and readily available clinical measurements, while adjusting for potential confounders such as residual femur length (derived from CT data), overall residual limb length (measured from ischial tuber to distal end of the limb by caliper), contraction potential (tape measured as the difference of circumferential volumes during thigh muscle contraction and relaxation), and soft-tissue coverage (measured as a ratio between thigh and femur diameter). Partial correlation is a measure of the strength and direction of a linear relationship between two continuous variables whilst controlling for the effect of one or more other continuous variables (also known as “covariates” or “control” variables). Although partial correlation does not make the distinction between independent and dependent variables, the two variables are often considered in such a manner (i.e., you have one continuous dependent variable and one continuous independent variable, as well as one or more continuous control variables). If data is not approximately normal, we will use log transformations. Moderate-to-strong, significant correlations between research-grade and clinical data will be retained for empirical testing in aim 3.

#### Aim 3

Statistical analysis for aim 3 will involve two parts. First, the predictive model developed in aims 1 and 2 will be tested using data from 15 new participants (i.e., data not used to create the model). Second, we will compare the quantitative socket design to the current standard of care, in terms of patient outcomes and cost.

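### Peak plantar pressure and in-socket pressure enter aim 2 unscaled, and body weight is not a named confounder, so a between-person correlation between them can partly or wholly reflect body weight

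*Protocol article*

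**What the plan says.** Under the data-processing heading Plantar pressure, the article states: "Pressure readings from each of the 99 discrete sensors will be used to calculate total plantar pressure". The centre-of-pressure path is derived as well. Three plantar variables then go into aim 2: "The peak plantar pressure from foot strike to midstance and the medial-lateral and anterior-posterior excursion of the center of pressure during support will be included". The caption of Fig. 13 also describes a total: "Total plantar pressure during the support phase of gait for 6 steps".

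For the in-socket side, the section In-socket pressure states: "We will measure peak pressure and area under the pressure versus the time curve recorded by each in-socket pressure sensor". Values are averaged over steps for aims 1 and 2. No division by body weight is stated for either pressure.

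Hypothesis H2 of aim 2 is that "gait analysis will correspond to dynamic pressure distribution". Under Statistical methods {20a}, aim 2 uses partial correlation, "adjusting for potential confounders such as residual femur length (derived from CT data), overall residual limb length", contraction potential and soft-tissue coverage. Correlations that are significant and at least moderate go forward to aim 3.

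Eligibility {10} caps weight at 125 kg with no lower bound. The static radiographs, by contrast, are taken at set fractions of body weight (25%, 50%, 100%).

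**The concern.** Pressure summed over the whole sole follows the vertical load, and vertical load in stance follows body weight. Weight may also raise the pressure inside the socket. Two unscaled load measures are therefore to be correlated while a plausible common cause is left out. The four named confounders describe limb length, muscle and soft tissue; none is a measure of load.

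The correlation decides what happens next. It selects the clinical measures tested in aim 3, and Fig. 6 shows selected measures guiding the socket design. A measure selected because heavier people press harder in both places would be labelled a gait test. It would add little to a weighing scale, and on that evidence nothing would be known about whether it tracks the effect of a socket change on in-socket pressure.

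**Working it through.** The article gives no figure for this correlation, so there is nothing to reproduce. The check asks what correlation body weight alone could create.

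**Inputs from the article.** n = 30, alpha = .05, four named covariates, no scaling of either pressure.

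**Assumptions (not in the article).** Between-person coefficient of variation (CV) of weight W 15-20%; plantar peak = W × a, with a varying by 5-20%; in-socket pressure = W^g × b, with b varying by 15-50%; a, b and W independent and lognormal, so there is no gait link. The four covariates are unrelated to W. The exponent g is 0 (no scaling with weight), 1/3 (weak scaling, for example because limb area grows with weight) or 1 (proportional).

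**Threshold.** With 30 − 2 − 4 = 24 degrees of freedom, t = 2.064, and the critical |r| = 2.064/√(2.064² + 24) = 0.388. A significant result therefore already has |r| near 0.4 or more.

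**Formulae**, on the log scale with s² = ln(1 + CV²):
- r(plantar, weight) = √[s²_W/(s²_W + s²_a)]
- r(plantar, socket) = g·s²_W / √[(s²_W + s²_a)(g²·s²_W + s²_b)]
- chance of significance from Fisher's z, with standard error 1/√(30 − 4 − 3) = 0.2085

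**Worked case**, CVs 20% (W), 10% (a), 30% (b): s² = 0.0392, 0.00995 and 0.0862.
- Plantar with weight: √(0.0392/0.0492) = 0.89.
- g = 1: 0.0392/√(0.0492 × 0.1254) = 0.50. Then z = 0.549 against a threshold of 0.410, and (0.549 − 0.410)/0.2085 = 0.67, so about 75% of trials are significant.
- g = 1/3: 0.0131/√(0.0492 × 0.0905) = 0.20, about 16% significant.
- g = 0: r = 0, 5% significant.

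**Full range over the assumed CVs**

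| Socket pressure and weight | Spurious r | Trials significant |
|---|---|---|
| none (g = 0) | 0 | 5% |
| weak (g = 1/3) | 0.06-0.39 | 6-51% |
| proportional (g = 1) | 0.18-0.77 | 14% to nearly 100% |

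For g above 0, the low end is at CVs of 15% (W), 20% (a) and 50% (b), and the high end at 20%, 5% and 15%.

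The correlation of the plantar peak with weight itself is 0.95-0.97 when a varies by 5%, 0.83-0.89 at 10%, and 0.60-0.71 at 20%.

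**Levels against changes.** A simulation of 30 participants with 9 sockets each (plantar residual CV 10%, socket residual CV 15-50%) gave, at g = 1:
- participant means: mean r 0.31-0.69, significant in 42-99%
- change from baseline for one socket: r about 0, significant in 4-8%

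**After the fix.** With the plantar peak divided by weight, r is about 0 and 4-6% of trials are significant in every scenario. Dividing by weight or adding weight as a covariate gives about 4-7% in a further simulation.

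**The case against.** The strongest reply is that aim 2 may not compare people at all. The title speaks of within-subject effects, the design is a crossover, and Outcomes {12} says that outcomes are analysed as change from baseline across sockets. Weight hardly changes over one or two lab visits, so it cancels from a change. If changes are used, this reply stands and the problem nearly disappears. But the aim 2 text does not say so. Its named confounders are mostly fixed features of a person, which makes sense for levels between people and much less for within-person changes, and the processing sections enter averages, not changes.

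A reader might infer two stronger statements: that the plantar variable is in effect body weight, and that H2 will be supported whatever the truth. The documents support neither.
- In-socket pressure is local, from four 2 cm × 2 cm pads, and need not rise in proportion to weight. With g = 0 there is no inflation.
- The peak of the total is the natural reading, since no other pressure quantity is defined, but a single-sensor peak is not excluded. That would also be unscaled, though less closely tied to weight.
- H2 concerns gait analysis as a whole. Centre-of-pressure excursions, trunk lean and hip angles are also aim 2 inputs, and none is a load measure.
- Pace is self-selected and may differ between people. With 20% residual variation the plantar peak correlates only 0.60-0.71 with weight.

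Soft-tissue coverage may also track weight and absorb part of the effect. If one covariate correlates 0.7 with weight (an assumption) and socket pressure is proportional to weight, significant results in three settings fall from 33%, 82% and 96% to 16%, 51% and 78%. That weakens the inflation without removing it.

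Finally, the confounder list is open, and a fuller plan could add weight. That is fair. Still, the article does name its confounders and how each is measured, and the list commits to no measure of load.

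**Conclusion.** The point holds as a possible confounder of one correlation. As written, peak plantar pressure and in-socket pressure are both unscaled and body weight is not a named covariate. A between-person correlation between them could therefore be produced or inflated by weight and be carried into aim 3.

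The size cannot be fixed from the article. It runs from no effect to near-certain false selection, and it turns mainly on three unknowns: how local socket pressure scales with weight, how much each pressure varies for other reasons, and whether aim 2 analyses levels or changes. The finding does not show that H2 as a whole is compromised, and it does not touch the other two plantar inputs. It is still worth correcting before analysis, because the remedy is specific, uses a value the trial already needs, and returns the false-selection rate to about 5% under every assumption tried.

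**What to change.** 1. In the data-processing section Plantar pressure, state that the peak is that of the 99-sensor total, and express it per body weight.
2. In the aim 2 paragraph of Statistical methods {20a}, add body weight to the adjustment set for every pair involving plantar or in-socket pressure.
3. In the same paragraph, state whether aim 2 correlates levels between people or within-person changes from baseline.

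The cost is wording and one degree of freedom. With five covariates and 23 degrees of freedom, t = 2.069 and the critical |r| = 2.069/√(2.069² + 23) = 0.396, against 0.388 now. No new measurement is needed: weight is already required for the eligibility limit and for setting the static load steps.

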**Fig. 13 Fig13:**
[figure not shown]
Plantar pressure measurements. **A** Total plantar pressure during the support phase of gait for 6 steps. **B** The path of the center of pressure during gait over 6 steps, superimposed on an outline of the foot

##### Tissue stiffness

The average tissue stiffness for each of the four regions of the residual limb will be included in the aim 2 analysis.

##### Body kinematics

Trunk lean and hip flexion/extension during gait will be calculated from the conventional motion capture system (marker-based) for at least 6 steps per trial of treadmill walking. Body angles will be calculated using markers placed on the shoulders, C7, hips (ASIS and PSIS), greater trochanters, knee (or flexion axis of the prosthesis), ankle, and foot. We will determine the average of peak trunk lean and the average peak hip flexion and extension over all steps and all trials for each prosthesis. The average values will be included in the aim 2 analysis. Qualitative gait analysis will be performed by 3 investigators using the webcam videos to classify the participant’s gait asymmetry in terms of magnitude and timing.

##### Static radiographs

The distance from the most distal point of the residual femur to the inside surface of the socket under each weight-bearing condition will be measured using the freely available ImageJ software. Measurements will be performed by 3 researchers independently, with the middle value of the three measurements used for aim 2 analysis.

##### Hip strength

Peak hip strength and ROM will be recorded directly from the hand-held dynamometer and the goniometer. Strength and ROM will be measured three times, with the middle value of the three measurements used for aim 2 analysis.

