### Eligibility criteria {10}

We aim to work with a representative, yet homogeneous sample of transfemoral amputees. All prosthesis users will have been ambulating with a prosthetic for at least 1 year. All participants will be under 125 kg of body weight. The amputation risk in males is 1.7 (dysvascular) to 4.9 (traumatic) times greater than in females [32], and our sample is assumed to be representative of that distribution. A weight limit of 125 kg is typical for most standard prosthesis componentry. Participants will be between 18 and 80 years of age and must be able to walk unassisted on a treadmill. Pregnant women will be excluded from the data collection to avoid the risk of exposure to ionizing radiation. An additional inclusion criterion for the participants in the pilot clinical trial is that they will be in need of a new socket.

The cause of limb loss will not be considered as an inclusion criterion, as the principal mechanisms under investigation apply irrespectively of the amputation cause. It may be possible to investigate any differences by etiology in post hoc analysis. Likewise, the residual limb length will not be considered as an inclusion criterion but will be documented and analyzed as appropriate post hoc.

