##### Hip strength and ROM

Hip abductor and flexor strength will be measured with a hand-held dynamometer (HHD) (Lafayette Instrument, Lafayette, IN) using previously established protocols [40] modified for amputees. Hip abductor strength will be measured with the participant side-lying on an examination table with the test hip facing up (Fig. 9). The non-test leg is bent at the hip and knee for stability. The test hip is in neutral flexion/extension and rotation. The moment arm is recorded as the distance in centimeters between the greater trochanter and the HHD. A non-elastic strap is used to secure the dynamometer against the leg and provide resistance to hip abduction. The strap is wrapped around the leg and underneath the table. The participant is asked to push up against the HHD as hard as possible for 4 s (substantial reliability; ICC .95) [41]. This procedure will be repeated to test hip flexor strength with the participant supine on the exam table and arms across the chest. Hip range of motion will be measured with a standard long-arm goniometer during active (moved by the participant) and passive (assisted by the tester) movements with the participant standing upright using crutches to balance.

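### Hip strength enters aim 2 as the direct dynamometer reading, and the moment arm that would turn it into torque is recorded but never used

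*Protocol article*

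**What the plan says.** Under Hip strength and ROM, abductor strength is tested with a hand-held dynamometer (HHD) held by a strap: "A non-elastic strap is used to secure the dynamometer against the leg and provide resistance to hip abduction". The lever is measured: "The moment arm is recorded as the distance in centimeters between the greater trochanter and the HHD". The flexor test repeats the procedure. No fixed distance or landmark for the dynamometer is given.

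Under Hip strength, in the data processing part, the analysed value is defined: "Peak hip strength and ROM will be recorded directly from the hand-held dynamometer and the goniometer". The next sentence adds: "Strength and ROM will be measured three times, with the middle value of the three measurements used for aim 2 analysis". No section multiplies the reading by the moment arm or mentions hip torque.

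Under Eligibility criteria {10}, "the residual limb length will not be considered as an inclusion criterion but will be documented and analyzed as appropriate post hoc".

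Under Statistical methods {20a}, Aim 2 uses partial correlation, described as a measure of linear association. The listed adjustment variables include residual femur length from CT and overall residual limb length from ischial tuber to distal end. Data that are not approximately normal are to be log-transformed. Correlations that are significant and at least moderate go forward to aim 3.

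**The concern.** A dynamometer strapped to a limb registers force. The muscle property of interest is the torque about the hip, which is force times lever. If the analysed score is the reading alone, two people with the same hip torque get different scores whenever the dynamometer sits at different distances from the joint: the shorter lever scores as stronger. The sample admits any residual limb length, so levers are likely to differ, and measuring the lever in each participant makes sense only if they do.

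Two things are at stake. In aim 2, a real link between hip strength and in-socket mechanics is diluted, which makes it less likely to pass the screen. In aim 3, if hip strength is retained, its value for a new participant would mix strength with lever length. The length adjustment belongs to the aim 2 correlation, and no length correction of the score itself is stated for aim 3.

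**Working it through.** The article states no figure on this point, so there is none to reproduce.

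**1. Lever effect at equal torque.** Force = torque / moment arm, so the ratio of two readings at equal torque is the longer arm divided by the shorter. The article gives no range of arms; the ranges and the torque of 60 Nm below are assumptions.

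- 20 and 25 cm: 60/0.20 = 300 N, 60/0.25 = 240 N, ratio 1.25
- 20 and 30 cm: 300 N, 60/0.30 = 200 N, ratio 1.5
- 15 and 30 cm: 60/0.15 = 400 N, 200 N, ratio 2.0
- 10 and 30 cm: 60/0.10 = 600 N, 200 N, ratio 3.0

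With torque as the score the ratio is 1.0 at any arm.

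**2. What the planned adjustment leaves.** A simulation of 400,000 draws took an outcome correlated 0.5 with log torque, uniform moment arms, a torque coefficient of variation (CV) of 0.2 or 0.3, and limb length equal to the arm plus noise with SD 1.5 cm. Correlations with the outcome were:

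| Arm range, cm | Torque CV | Force, unadjusted | Force, adjusted | Log force, adjusted | Torque, adjusted |
|---|---|---|---|---|---|
| 20-30 | 0.2 | 0.425 | 0.475 | 0.483 | 0.496 |
| 20-30 | 0.3 | 0.451 | 0.477 | 0.491 | 0.488 |
| 15-30 | 0.2 | 0.346 | 0.456 | 0.474 | 0.496 |
| 15-30 | 0.3 | 0.402 | 0.467 | 0.489 | 0.490 |
| 10-30 | 0.2 | 0.259 | 0.413 | 0.460 | 0.497 |
| 10-30 | 0.3 | 0.323 | 0.434 | 0.477 | 0.488 |

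Adjustment recovers most of the loss. In the 15-30 cm, CV 0.2 row, the shortfall against torque is 0.496 - 0.346 = 0.150 before adjustment and 0.496 - 0.456 = 0.040 after it.

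**3. Placement that does not track limb length.** The adjustment variables are femur length and limb length, not the trochanter-to-dynamometer distance. A second simulation used n = 30, limb length 15-35 cm, torque CV 25%, a true correlation of 0.5 and 4,000 runs. Placement varied around a fixed fraction of limb length. Adjusted for limb length:

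- torque: r = 0.49, power 80-81%
- force, placement scatter 0%: r = 0.46, power 76%
- force, scatter 10%: r = 0.43, power 69%
- force, scatter 20%: r = 0.36, power 50%

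With placement tracking limb length, other plausible settings give adjusted force of about 0.47 to 0.49. The overall span for adjusted force is therefore roughly 0.36 to 0.49, against about 0.49 for torque.

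**4. The unadjusted score.** At 15-30 cm and CV 0.2, raw force correlates 0.70 with true torque and -0.69 with the moment arm. A raw score used as a predictor outside the adjusted aim 2 correlation would, under these assumptions, reflect lever length about as much as strength.

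**The case against.** The strongest reply is that torque was intended. The article names the distance a moment arm, which has little use except to compute torque. The phrase about direct recording may describe data capture, and the conversion could sit in the full protocol. The middle of three readings fits torque too, since with one fixed arm the median force times the arm is the median torque. This is a fair guess at intent. But the paragraph does more than omit a detail: it says which value is analysed, and that value is the instrument reading. If torque is meant, the sentence needs the same correction.

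The second reply is that the aim 2 adjustment already deals with length. This largely stands when placement follows limb length. The provision for log transformation helps as well, because log force = log torque - log arm; but it applies only if the data look non-normal, and it does not supply the actual dynamometer distance.

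The third reply is that little depends on it. Hip strength is absent from the aim 2 hypotheses and from the outcome list, the trial is called exploratory, and no aim 3 predictor using hip strength is specified. This stands and limits the weight of the point.

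A reader might also infer that scores are distorted two-fold, or that length effects would often pass as strength effects. The documents support neither. They give no lever range. A simulated false-positive rate of 36-46% for force with no true strength link arises only without length adjustment, and that is not the planned analysis.

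**Conclusion.** The point holds in a limited form. As written, the aim 2 hip strength variable is a lever-dependent reading, and the recorded quantity that would remove the dependence is not used. The planned length adjustment takes out most of the distortion in aim 2 if the dynamometer is placed in proportion to limb length. What remains comes from the reciprocal relation to the lever and from placement differences. The fall to about 0.36 needs 20% placement scatter, an assumption with no support in the article either way. The two-fold difference in readings is likewise only an example, for levers of 15 to 30 cm. The consequence for aim 3 is conditional on hip strength passing the aim 2 screen. This is a minor improvement that costs nothing in data collection, and it does not threaten the trial's main conclusions.

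**What to change.** In the Hip strength paragraph, define abductor and flexor strength as dynamometer force times the recorded moment arm, in Nm, with the arm converted from centimetres to metres. Take the middle of the three torque values, and use torque in the aim 2 analysis and in any aim 3 predictor. If force is preferred, say so and give the reason.

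The cost is one line of derivation. The moment arm is already recorded for the abductor test, and the flexor test repeats that procedure, so no measurement is added.
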